#### Tumoural immune infiltration

4.8.8

Immune reaction will be described by percentage by lymphocyte type. These proportions will be compared to corresponding microbiota characteristics: for example lung microbiota and lung tumour. Statistical association between these parameters will be tested as in the previous paragraph.

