### Evaluation of tumour immune infiltrate

4.3

Immunohistochemistry will be performed on tumour tissue using the specific antibodies to detect subpopulations of immune cells as follows: cytotoxic T-lymphocytes (anti-CD8, clone SP16, ThermoFisher Scientific), regulatory T-lymphocytes (anti-FoxP3, clone SP97, ThermoFisher Scientific), B-lymphocytes (anti-CD20, clone SP32, Cell Marque). The immune response checkpoint axis PD-1–PD-L1 will be assessed by anti-PD-1 (clone NAT105, Cell Marque) and anti-PD-L1 (clone 28-8, Abcam). All staining will be performed by a fully automated, standardised procedure (Benchmark XT, Ventana/Roche). The number of lymphoid cells expressing each antigen, except PD-L1, will be determined within 5 consecutive x40 microscopic fields, starting from the invasive front toward the tumour centre, used as a parameter reflecting the tumour's quantity of a given immune cell subpopulation. PD-L1 will be assessed for both immune and tumour cells and reported as the percentage of each population expressing the antigen.

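### Tumour infiltrate is measured as cell counts (section 4.3) but tested against the microbiota as percentages with no stated denominator (section 4.8.8), so the planned test ignores the amount of infiltration

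*Protocol article*

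**What the plan says.** **Measurement (section 4.3, Evaluation of tumour immune infiltrate).** Tumour sections are stained for CD8, FoxP3, CD20, PD-1 and PD-L1. For all but the last, the readout is a number: "The number of lymphoid cells expressing each antigen, except PD-L1, will be determined within 5 consecutive x40 microscopic fields". The section says what the number is for; it is "used as a parameter reflecting the tumour's quantity of a given immune cell subpopulation". PD-L1 is the exception: "PD-L1 will be assessed for both immune and tumour cells and reported as the percentage of each population expressing the antigen".

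**Analysis (section 4.8.8, Tumoural immune infiltration).** "Immune reaction will be described by percentage by lymphocyte type". The section then sets these proportions against the corresponding microbiota, with lung microbiota and lung tumour as its example. The test is carried over from section 4.8.7: Pearson or Spearman correlation with FDR correction. Section 4.8.9 makes tests two-sided at 0.05.

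**Place in the objectives.** The introduction's objective (iii) concerns the effect of microbiota composition on immune and inflammatory status, including in the lung. Characterising the tumour infiltrate is part of the secondary outcomes in section 2.2.

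**The concern.** The two sections use different scales, and nothing links them. Section 4.3 produces an amount; section 4.8.8 describes and tests a composition. A percentage on any lymphocyte denominator divides out how many cells there are. A sparsely and a heavily infiltrated tumour with the same mix then look identical.

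What is at stake is one component of a secondary objective. If the microbiota relates to how densely a tumour is infiltrated, and not to which lymphocytes make up the infiltrate, the analysis as written would not show it, although the data to show it will be in hand. In addition, because the denominator is unstated, two analysts could derive different percentages from the same slides.

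**Working it through.** The document gives no figure for this endpoint, so there is nothing to reproduce. The check sets the sections side by side and then uses small examples. All counts and simulation settings below are assumptions.

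**1. Scale of each tumour readout**

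| Marker | Readout in section 4.3 | Scale in section 4.8.8 |
|---|---|---|
| CD8, FoxP3, CD20 | number of positive cells, five fields | percentage |
| PD-1 | number of positive cells, five fields | not mentioned separately |
| PD-L1 | percentage of immune cells and of tumour cells | not mentioned; not a lymphocyte type |

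No analysis of the counts is specified in section 4.8.8 or elsewhere in section 4.8.

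**2. Denominator.** A percentage by lymphocyte type needs a lymphocyte total. The tissue panel in section 4.3 has no CD3, CD4 or CD45 stain, and no total lymphoid count is described. CD3 and CD4 appear only in section 4.4, which is flow cytometry of blood and BALF. So the denominator for tumour tissue is unspecified.

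**3. What the percentage scale removes.** Percentage of type i = 100 × count of type i / total. Taking CD8 + FoxP3 + CD20 as the total, purely for illustration:

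- Counts 10/5/5, total 20: 10/20, 5/20, 5/20 = 50/25/25%.
- Counts 500/250/250, total 1,000: 500/1,000, 250/1,000, 250/1,000 = 50/25/25%.

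The totals differ by 1,000/20 = 50-fold and the percentages are identical. A larger denominator gives the same result if the unstained lymphocytes scale with the stained ones.

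**4. What the missing denominator changes.** Take CD8 = 60, FoxP3 = 20, CD20 = 40, a stained sum of 120. The CD8 percentage is:

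- 60/120 = 50% of the stained cells;
- 60/(120 + 60) = 33% if 60 unstained lymphocytes are included;
- 60/(120 + 120) = 25% if 120 are included.

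**5. Effect on the planned test.** A simulation of 4,000 runs per sample size used these assumptions: a microbiota feature correlated 0.5 with the log of total infiltrate (log mean 5, SD 0.7); cell shares independent of the feature (Dirichlet 8, 3, 6); Poisson counts; Spearman test of one cell type, two-sided 0.05, without FDR correction.

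| Patients | Power, count | Power, percentage of stained cells |
|---|---|---|
| 20 (one group) | 49% | 5% |
| 40 (both groups) | 83% | 5% |

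The 5% is the false-positive rate, as it must be when composition is set independent of the feature. The table shows what happens when only the amount varies with the microbiota; it says nothing about how likely that is in these patients. Using Spearman in place of Pearson does not help, because the amount is gone before the ranks are formed.

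**The case against.** The strongest reply is that the document contains a wording mismatch and little more. Section 4.3 counts lymphoid cells positive for each antigen, so lymphoid cells are recognised apart from the stain, and PD-L1 is reported as a percentage of immune cells without any pan-leucocyte antibody. A morphological lymphocyte total is thus conceivable, and the full protocol or SAP may define it. Composition is a legitimate question in its own right. The counts are collected, the study is exploratory, and section 4.8.9 allows complementary analyses.

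Much of this stands, and it rules out several stronger readings:

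- A reader might infer that no denominator can be obtained. The document supports only that none is stated.
- A reader might infer that the percentages must sum to 100, so that cell types are pushed into negative correlation with each other (−1/(k−1) = −0.5 for three exchangeable parts). That requires CD8 + FoxP3 + CD20 as the denominator, which the document does not say. If each marker were a percentage of all lymphoid cells, the values need not sum to 100. The −0.5 also concerns pairs of cell types, which section 4.8.8 does not test.
- A reader might infer that the amount of infiltration is lost to the study. It is left out of the planned test; the data set keeps it.

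The reply does not remove the core. Whichever lymphocyte denominator is chosen, a percentage discards amount. The allowance for complementary analyses does not commit anyone to analysing counts. Nor is this a detail left out by condensing: the article states both scales, and they disagree.

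**Conclusion.** The point holds in this form: section 4.8.8 tests a variable other than the one section 4.3 measures, with no stated denominator, and so cannot detect an association between the microbiota and the amount of infiltration when the cell mix is unchanged. That follows from the two sections alone. Its practical size does not: the 50-fold example and the power figures rest on invented inputs and illustrate the mechanism only. The matter should be corrected, but it affects one part of a secondary objective in an exploratory study and touches neither the primary outcome nor the sample size.

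**What to change.** In section 4.8.8, and in any separate analysis plan that repeats it:

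- use the section 4.3 counts over the five fields for CD8, FoxP3, CD20 and PD-1 as the infiltrate variables in the correlation with microbiota, either rank-based or after log transformation;
- keep percentages for PD-L1 on tumour and immune cells, as section 4.3 measures it;
- if lymphocyte percentages are kept as a supplementary measure of composition, state their denominator and how it is obtained.

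This takes a sentence or two. The counts are already planned, so using them needs no new staining or sampling. The downside is a few more tests under the existing FDR correction if both counts and percentages are analysed.

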#### Complementary analyses

4.8.9

Complementary analyses will be performed if particular biological issues can be better described.

All statistical analyses will be performed using R-software version 3.5.0 or later (R-Project, GNU GPL). Tests will be 2-sided and the significance threshold is set at 0.05, after FDR correction where needed (as for the analyses concerning taxonomic ranks below phylum). Data may be missing due to possible loss of follow-up between inclusion and end of study. A description of the missing data and associated reasons will be given.

### Data monitoring committee

4.9

A data monitoring committee is not needed in this study since this is an observational trial and there are no intervention or security risks for patients.

## Discussion

5

### What is known

5.1

Lung cancer is a leading cause of death by cancer worldwide, responsible for 1,761,007 or 23.1% deaths in 2018 according to the WHO.^[56]^ It is also the most frequent cancer in men and the 3rd most frequent in women.^[56]^ While well characterised regarding its aetiology, morphological, and molecular properties,^[57–59]^ much less is known regarding its relationship with lung microbiota, and almost nothing regarding its connection to distant sites such as the gut and gut microbiota. This lack of studies is self-explanatory when one knows that not so long ago lungs were considered sterile except in case of infection.^[55,60]^ Recently, however, there is an emerging idea of more “systemic” influence of the gut microbiota, and its connection to the immune system beyond the local effect.^[3,60–62]^ A few teams made a huge leap in elucidating the role of the gut microbiota in chemotherapy and anticancer treatment, including lung cancer.^[63–67]^

### What is new

5.2

Based on these studies and the questions unanswered, we designed a case-control observational trial underlining a multi-aspect approach to the patient. In each of our subjects, we decided to characterise the microbiota of different sites (UAs, gut, and lung microbiota), in parallel with immune profile characterisation (local and systemic) while taking into account the patient's life style (nutrition, smoking status, profession, etc.). Examination of these factors in patients undergoing chemotherapy before surgery enables a direct follow up of these parameters correlated with the treatment phase (to our knowledge, this has never been reported for lung cancer before). Moreover, lung microbiota at surgery is sampled in 2 ways: by performing broncho-alveolar lavage (BAL) directly on the excised lung lobe (to eliminate possible UAs contamination and obtain the maximal microbial concentration for analysis), and by sampling lung tissue at 3 sites: “healthy” tissue distal to tumour (used as a control tissue),^[12]^ peritumoural tissue, and tumour itself. This enables sampling of both luminal and tissue/cell-bound bacteria which, according to known studies, do not share the same microbial composition.^[26]^ To our knowledge, at present there is no study of lung cancer that examines the microbiota of peritumoural tissue, and even less in 4 different lung sample types. Also, no study performed BAL directly on the tumour lobe without passing through the UAs.

### Choice of analyses

5.3

As previously reported, certain bacterial species can modify our immune responses differently, such as *Faecalibacterium prausnitzii* or on the other hand *Fusobacterium nucleatum*, as well as the whole cluster (*Clostridia* cluster XIV).^[68,69]^ Therefore, tumour lymphocyte infiltration and lymphocyte composition in the broncho-alveolar lavage fluid (BALF) will be examined and closely looked at for its relationship with sampled microbiota. Likewise, each tumour is characterised according to the TNM stage classification^[70]^ and histological properties. Tumour architecture, localisation in the lung, and disease severity are expected to dynamically interact with microbial composition in situ and immune profile, as seen in similar pathologic states of the lung (obstruction of the normal lung architecture, creation of anaerobic thermal pockets in the case of bronchial obstructiveness, immunogenicity of the tumour, promotion of neutrophil recruitment, inflammation).^[12,15,71–73]^ Difference of the microbiota composition between tumour samples of adenocarcinoma and squamous cell carcinoma has already been evidenced by Yu et al.^[15]^ Interestingly, salivary microbiota is also proven to correlate with NSCLC type.^[40]^ Therefore, similar analysis direction will be taken with our salivary and lung samples.

As mentioned, intestinal microbiota has both local and systemic influence on its host. According to the gut-lung axis theory,^[4]^ bacteria or their products might have systemic effects, and therefore, have an effect on the lung microbial composition and immune response. For this reason, faecal microbiota will be characterised, as well as faecal SCFAs concentrations (known products of bacterial fermentation and immune modulators/protectors of the intestinal barrier).^[74]^ The SCFAs might be potential mediators of the gut's “long-distance” influence by direct effect on the target site or indirectly via gut/circulating immune system stimulation. As intestinal microbiota is shown to adapt very quickly to the changes in nutrition, as well as its influence on SCFAs concentrations,^[22,75]^ nutritional records before each faecal sampling will be taken into account. We will not only determine the composition of faecal microbiota, but also its “quality” and influence on intestinal health by dosage of bacteriocins (HNP1-3, β-defensin 2), and calprotectin as inflammatory marker.^[76]^ Broad-spectrum cytokine profiling and immune cell phenotyping in the blood will be used to evaluate systemic immune status. This holds particular importance as connection to circulating IL-6 and IL-8 was previously reported in lung cancer,^[76,77]^ but also to intestinal SCFA concentrations.^[78]^

As explained, group Pct-chir will enable follow-up on multi-site microbiota and immune status during different treatment phases (Fig. 1). Since the biggest problem of chemotherapy, despite its efficacy against tumour cells, is its non-selectivity (effecting epithelial layers and mucosae),^[79–81]^ we expect to see changes in all 3 types of microbiota—salivary, faecal, and lung, as all are closely related to epithelial and mucosal layers. Similarly, immune characteristics should be altered following the chemotherapy and above-mentioned changes in microbiota (but also vice versa—the affected immune system will change its interaction with microbiota, thus modifying it). Finally, we could hypothesise that different initial properties of the tumour (why the patient is prescribed chemotherapy or not in the 1st place) might divide 2 patient profiles (Pchir vs. Pct-chir 1st time point) regarding both multi-site microbial and immune/inflammatory characteristics.

### Final word

5.4

To conclude, our results will be one of the 1st to give a better understanding of the close and intense interaction between the microbiota of different, yet communicating sites and their interaction with the immune system in patients suffering from lung cancer (the world's number 1 cause of death by cancer).^[82]^ The strength of this study design is data collection through multiple non-invasive techniques that can be incorporated into the standard medical care and treatment of the patients. Another strong point is a multi-site approach towards each patient: lifestyle, nutrition, immune status, and microbial composition are assessed using different and complementary techniques (e.g. faecal microbiota will be assessed by techniques of molecular biology via qPCR and sequencing, but also by bacterial culture, and in the aspect of individual's nutrition). The main limitation is lack of the “healthy” control group, not authorised by Ethics Committee because of the invasiveness of the sampling techniques for healthy subjects. Therefore, previously published data on healthy subjects and similar cohorts will be addressed only in a descriptive matter, while we will focus more on relational aspects (e.g. interaction between site-specific immunity and its microbiota).

We hope that our results will help in setting the basis for developing more personalised or “alternative” approaches in lung cancer treatment, better characterisation of patient's status and diagnosis, as well as in finding ways of improving chemotherapy tolerance and effectiveness (complementary prebiotics, probiotics or symbiotics).
